## Abstract

Vaccine coverage and disease surveillance data are valuable for monitoring protection against vaccine-preventable diseases; however, they do not directly measure population immunity. High-quality, representative serological studies can provide key insights into immunity gaps, outbreak susceptibility, and inform targeted vaccination strategies, even in high-performing immunization programs. This study aims to estimate location-specific and age-specific immunity profiles for measles and rubella while evaluating the predictive value of indirect immunity estimates derived from vaccination and surveillance data against direct serological measurements. Additionally, it seeks to model the risk of measles outbreaks and assess the impact of mitigation strategies. A multi-stage, stratified cluster sampling design will be implemented across six districts in The Gambia’s North Bank and Upper River Regions. Survey clusters (i.e. 5 km × 5 km areas) encompassing all settlements within their boundaries will be selected, proportionally to district population sizes. Cluster selection ensures representativeness of both the population and vaccine coverage within each district. Based on detecting a 10% difference in protective immunity across vaccine coverage levels, power analysis assumes an intraclass correlation coefficient (ICC) of 0.01. In each cluster, 70 children aged 9 months to 14 years will be recruited, yielding a total sample size of 1,750 children across 25 selected clusters. Dried blood samples will be collected and tested for anti-measles and anti-rubella IgG using enzyme immunoassays (EIA). District-specific measles seroprevalence will be estimated using a hierarchical spatial model. This study will generate key evidence needed to refine immunization strategies and reduce the risk of measles and rubella outbreaks.

## Background

Measles is highly contagious, requiring vaccination coverage rates and population immunity levels of 92–95% to prevent outbreaks or interrupt transmission [1]. However, despite high overall vaccination coverage rates, measles outbreaks can still occur due to factors such as waning immunity in certain age groups and untimely vaccination [2–4]. Thus, measles outbreaks serve as a sensitive indicator of emerging immunity gaps, even in populations with otherwise high vaccination coverage. The World Health Organization (WHO) African Region aimed to eliminate measles and rubella by 2020 [5,6]. However, transmission persists, with repeated measles outbreaks occurring even in countries that have achieved high vaccination coverage through routine and supplementary immunization activities (SIAs) [5]. While these outbreaks may be self-limiting, those who do become infected can suffer severe long-term complications, including blindness, deafness, and immune system impairment [7]. In the short term, immune system effects can persist for months, leaving children vulnerable to other serious infectious diseases [8].

Rubella infection, on the other hand, is typically asymptomatic or presents as a mild illness, which makes it difficult to detect and often leads to underreporting [7]. In African settings, the herd immunity threshold required to interrupt rubella transmission is estimated to be between 85% and 91% [9]. Failure to achieve this level of immunity in childhood increases the average age of infection, leaving women vulnerable to rubella infection during their reproductive years. This vulnerability heightens the risk of exposure and infection during pregnancy. Primary rubella infection during early pregnancy can have severe consequences, including miscarriage, stillbirth, or the birth of a child with congenital rubella syndrome (CRS), which carries serious public health implications [10]. The primary goal of rubella vaccination is to prevent CRS, with the WHO estimating that 100,000 CRS cases occur globally each year [11].

The Gambia achieved a global milestone in 1967 for being the first country to successfully interrupt measles transmission [12]. To sustain this achievement, the country launched its Expanded Programme on Immunization (EPI) in 1979, initially including the measles vaccine among seven core vaccines [13]. Routine first-dose measles vaccination (MCV1) was introduced at nine months of age [13], with a vaccine effectiveness (VE) of ~95% [14]. A second dose (MCV2), with a reported VE of ~99% [14], was implemented in 2012 [15], targeting children at 18 months. In 2017, the country switched from a measles-only vaccine to a combined measles/rubella vaccine (MR) for both MCV1 and MCV2 due to epidemiological evidence of rubella in the population. The Gambian EPI continues to be a model for sub-Saharan Africa, maintaining high routine vaccination coverage rates comparable to high-income countries. In the years leading up to the COVID-19 pandemic, the country consistently achieved MCV1 coverage rates exceeding 90%; however, MCV2 coverage consistently declined from a high of 81% in 2015, to 52% in 2022 [16]. Additionally, six SIAs for measles and rubella have been conducted since 2002 at intervals of 4–6 years, mostly targeting children aged 9 to 59 months. Coverage for all SIAs exceeded 91%, except in 2022, when it dropped to 53% [17]. This decline prompted a repeat SIA in 2023, which successfully reached a coverage rate of 88.4% [18].

Recent measles outbreaks in The Gambia highlight the need for further investigation, especially considering the substantial progress the country had made toward the WHO measles and rubella elimination milestones by 2019 [19]. By mid-2023, there was a six-fold increase in measles cases compared to 2020 figures (Figure 1A) [20,21], despite historically high MCV1 coverage, the introduction of MCV2 for about a decade, and regular SIAs. Between 2014 and 2023, The Gambia reported 261 confirmed measles cases, with most cases occurring among children aged 1–4 years (35.2%), 5–9 years (33.0%), and under 1 year (12.3%) [20]. Additionally, 21% of all cases were reported among children who had received MCV1 (Figure 1B) and were mostly clustered in specific districts across the country (Figure 1C). Evidence suggests that the potential for measles outbreaks might be higher than expected in areas where there is geographic clustering of under-vaccinated children, even in settings with high overall measles vaccine coverage [22]. Previous studies from the US [2], Malawi [23], and The Gambia [3] have demonstrated that measles outbreaks can occur even with high overall vaccination coverage rates. This highlights the importance of thoroughly mapping population immunity profiles and predicting outbreak susceptibility across different locations and age groups in the country.

**Figure 1. f0001:**
[figure not shown]
(A) Annual measles incidence rate per million population in the Gambia, 2011–2023; (B) Vaccination status of confirmed measles cases in the Gambia, 2014–2023; (C) Measles case distribution by district and year across the seven health regions in the Gambia. Note: The red horizontal dashed line is the WHO threshold for measles elimination of ≤ 1 case per million population. Data source: Gambia measles case-based surveillance database. CRR = Central River Region, LRR = Lower River Region, NBER = North Bank East Region, NBWR = North Bank West Region, URR = Upper River Region, WR1 = Western Region 1, WR = Western Region 2.

A key challenge in understanding infectious disease dynamics is accurately defining the landscape of population immunity and susceptibility to outbreaks [14,24]. Although vaccine coverage and disease surveillance data are often used to monitor population immunity levels and identify susceptible subpopulations, these data sources do not directly measure immunity across age and space [14,25]. Issues such as overestimated vaccination coverage rates from administrative or survey-based data, along with under-reported cases due to poor surveillance systems, can lead to an overestimation of immunity [14,26]. This can result in masking of immunity gaps and clustering of outbreak risk within specific subpopulations – a problem observed in many low-income countries, including The Gambia.

High-quality, representative and geographically diverse serological surveys provide the most direct and accurate method for defining the immunity landscape [27]. Serological surveys are useful in predicting outbreak susceptibility, and informing targeted vaccination strategies, particularly when longstanding immunity gaps are suspected in specific age groups or sub-populations [26]. These surveys can help resolve uncertainties and identify when, where, and in whom immunity gaps are significant. Despite their value, serological surveys are underutilized due to logistical challenges [28], lengthy implementation times, and the lack of reliable, representative sampling frames [14]. Additionally, obtaining representative samples can be difficult, and it is rare to have access to critical metadata, such as immunization records, alongside available samples [29]. Cost concerns also make serosurveys less feasible in low- and middle-income countries (LMICs) [24], where they have been conducted less frequently [30]. The WHO recommends less invasive methods, like dried blood spot collection, for large surveys as these simplify specimen collection, lower costs, and improve participation [14]. However, venous blood collection, the gold standard, is more invasive and may reduce survey uptake. Our unique access to the health and demographic surveillance systems (HDSSs) in The Gambia provides an opportunity to overcome some of these challenges.

## Methods

### Study aim and objectives

The main aim of this study is to investigate the population-level measles and rubella immunity gaps across age and spatial location across two regions in The Gambia. The findings will help predict outbreak susceptibility and inform targeted vaccination strategies aimed at measles and rubella elimination in the country.

The primary objectives are;
To estimate the age-specific and location-specific immunity profiles for measles and rubella across two regions in The Gambia.To evaluate the predictive value of indirect estimates of measles and rubella population immunity (based on vaccination and surveillance data) compared to direct immunity measured through cross-sectional serological data.To model the risk of a measles outbreak across different age cohorts and spatial locations in The Gambia based on seroprevalence data.

The secondary objectives are;
To assess the impact of mitigation strategies, such as adjustments to routine vaccination and supplementary immunization activities, on the modeled risk of a measles outbreaks.To compare seroprevalence levels determined using dried blood spots versus venous blood specimens for estimating measles and rubella seroprotection in The Gambia.

### Study design

This study is a cross-sectional serological survey to estimate measles and rubella immunity gaps across age and spatial location in The Gambia.

### Study setting and population

The study will be conducted within the Basse and Farafenni Health and Demographic Surveillance Systems (BHDSS and FHDSS), located in the Upper River and North Bank Regions (URR and NBR) of The Gambia, respectively (Figure 2). The BHDSS and FHDSS collectively monitor approximately 250,000 individuals, representing about 10% of the country’s population [31]. With a combined annual birth cohort of about 8,000 infants, both HDSS sites conduct routine surveillance rounds every four months, collecting comprehensive health information, including vaccination and disease data from all consenting households within the communities.

**Figure 2. f0002:**
[figure not shown]
Spatial locations of villages/settlements in the Basse and Farafenni Health and demographic surveillance systems (HDSS) located in the Upper River and North Bank Region of the Gambia.

The geographic location and population covered by both HDSS sites present a unique opportunity to gain insights into the dynamics of measles and rubella. Notably, disease surveillance data show that NBR, home to the FHDSS, reported the second-highest number of measles cases in 2022, surpassed only by the more urban Western Region. By 2023, NBR recorded the highest number of measles cases in The Gambia (Figure 1C). This highlights the critical need to implement serosurveillance in this part of The Gambia to better understand immunity gaps across different age groups and at finer spatial scale. Additionally, our previous research has identified URR, where the BHDSS is situated, as one of the two regions with the highest rates of delayed MCV1 [32], further justifying the implementation of serosurveys in these areas.

For this serological survey, we will recruit children aged nine months to 14 years, categorized into four age cohorts: < 1 year, 1–4 years, 5–9 years, and 10–14 years. This stratification aligns with disease surveillance data indicating higher measles prevalence within this age range in The Gambia [20]. It enables a detailed analysis of serological profiles across age groups, providing key insights for The Gambia immunisation program to inform targeted vaccination strategies.

### Sampling strategy and sample size

#### Methodological overview

We integrated geospatial data and demographic projections (i.e. population and age categories) to establish a robust sampling frame for children aged 9 months to 14 years in the two HDSS sites (i.e. the BHDSS and FHDSS). Our approach combines:
Choropleth Map: Derived from the 2019–2020 Gambia Demographic and Health Survey (GDHS), this map models measles and rubella first-dose (MR1) vaccine coverage at 9 months across 5 km × 5 km raster grids for children aged 12–35 months. Each raster grid, assigned a uniform MR1 coverage, represents all settlements within that grid cell.Point Map: Obtained from the BHDSS and FHDSS, this map provides the geographical coordinates (longitude and latitude) of all settlements in BHDSS and FHDSS. The point map showing the settlements was overlaid on the choropleth raster map.

#### Population projection

We extracted population data from BHDSS and FHDSS as of January 2023:
BHDSS: Comprises 220 villages with 43,428 children 9 years and under (3,223 aged 0–1 years 25,608 aged 1–4 years, and 14,597 aged 5–9 years).FHDSS: includes 149 villages with 13,858 children 9 years and under (944 aged 0–1 year, 8,111 aged 1–4 years, and 4,803 aged 5–9 years).

Children aged 10–14 years will also be included in the serosurvey. Since data collection is scheduled for April – August 2025, we projected population sizes for each settlement using time series forecasting (*auto.ARIMA* models) applied to monthly HDSS birth data available through January 2023. These projections account for children aged 9 months to 14 years, ensuring that the sampling frame reflects anticipated demographic changes.

#### Sampling strategy

A multi-stage stratified cluster sampling design was employed across BHDSS and FHDSS. The sampling procedure occurred in four stages: stratification by site and district, selection of clusters, selection of households, and selection of children.

##### Stage 1: stratification by site and district

The study population is first stratified by HDSS site (i.e. BHDSS and FHDSS) and further by district within each site. There are a total of six districts: four in BHDSS and two in FHDSS.

##### Stage 2: selection of clusters

Survey clusters were defined as 5 km by 5 km land areas (25 km^2^), corresponding to the raster resolution of the modeled MR1 coverage from the 2019–2020 GDHS [33]. The primary sampling units (PSUs) are these clusters and includes all HDSS settlements within its boundaries. Clusters were selected within each district proportional to the district’s population size, ensuring that districts with larger populations contribute more clusters to the sample. Additionally, the selection process ensured that the combination of clusters were representative of both the population distribution and the overall MR1 coverage within each district.

For each cluster, let: ***a*** = the population size of the cluster; *b* = the cumulative population size of all clusters within a stratum (district); *c* = the predetermined number of individuals to be sampled from the cluster; and *d* = the total number of clusters to be sampled within the stratum (district).

The sampling interval (SI) per district is calculated as:$$\mathrm{SI}=\frac{b}{d}$$

To ensure randomness across districts, a random start (RS) between 1 and SI is chosen, and clusters are selected according to the arithmetic progression:$$n_{\mathrm{th}}\mathrm{value}=\mathrm{RS}+\left(n-1\right)\times \mathrm{SI}$$

using the cumulative population sizes to determine the sequence.

To adjust for potential sampling biases and to ensure that the sample is representative of the population, inverse probability weighting (IPW) was applied. The probability of selecting a cluster *(P*_*clust*_) and an individual within the cluster *(P*_*indiv*_) are computed as:

$P_{\mathrm{clust}}=\frac{a\times d}{b}$ and $P_{\mathrm{indiv}}=\frac{c}{a}$

Thus, the IPW for each individual is:$$\mathrm{IPW}=\frac{1}{P_{\mathrm{clust}}\times P_{\mathrm{indiv}}}$$

Clusters with fewer than 40 children aged 14 years or younger were excluded from the sampling frame to avoid selection bias and ensure statistical robustness. This threshold ensures that each selected cluster contributes sufficient data for meaningful analysis, particularly for the 1–4 years age group, which the study is powered by and is critical for assessing vaccine coverage and seroconversion following earlier MR1 and MR2 vaccination.

Following cluster selection, a statistical power analysis was conducted. This analysis, based on detecting a 10% difference in protective immunity between different MR1 coverage levels and assuming an intraclass correlation coefficient (ICC) of 0.01 was conducted using simulations on a high-performance computing (HPC) system. The sampling procedure was simulated 10,000 times, and the final sample consists of the top 5% of simulations with the highest statistical power (see supplementary Table S1). Figure 3 shows the map of the 25 selected clusters from the BHDSS and FHDSS.

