##### Stage 4: selection of children

From the selected households, a list of all eligible children will be made. To ensure adequate power and based on the simulations conducted, 70 children per cluster will be sampled from these households according to the following age group allocation: < 1 year (10 children); 1–4 years (40 children); 5–9 years (10 children); 10–14 years (10 children).

This allocation (ratio 1:4:1:1) was chosen because the study was powered based on the 1–4 years age group, which is key to assessing vaccine coverage and immunity profiles following MR1 and MR2. In households containing multiple children within the same age cohort, one child per cohort will be randomly selected, ensuring that no more than one child from each age group is chosen from the same household. Sampling in each cluster will continue until 70 children are recruited, yielding a total sample size of 1,750 children from 25 selected clusters. To avoid selection bias, the survey Statistician and Data Manager, instead of field teams, will be responsible for the selection of households and generating random list of children to be recruited from each cluster.

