### Statistical analysis and modeling

#### Descriptive analysis

We will use the R package *survey* to account for the complex sampling design when estimating age-specific and location-specific measles and rubella seroprevalence. Sampling weights will be applied to ensure representativeness, given the probability proportional to size sampling across the 25 randomly selected clusters. The weights will be computed based on the inverse probability of selection and will be adjusted to account for differences between the projected and actual population sampled per age group in each cluster.

Seroprevalence estimates will be generated for the four age cohorts (under 1 year, 1–4 years, 5–9 years, and 10–14 years) and across the sampled districts. We will report overall, HDSS level, district, ward, and age-specific seropositivity estimates. All 95% confidence intervals will be computed using linearized Taylor series variance estimation. We will use T-tests to assess the significance of differences in weighted seroprevalence between subgroups (e.g. age, sex, district). Associations between seropositivity and predictor variables (age, sex, geographic location) will be analyzed using univariate and multivariate generalized linear regression models, adjusting for the survey weights. Both unadjusted and adjusted odds ratios (ORs) with 95% confidence intervals will be reported.

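### The printed individual selection probability c/a does not describe how children are drawn, and no stated adjustment restores the within-household factor

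*Protocol article*

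**What the plan says.** All references are to the protocol article.

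- **Stage 2: selection of clusters.** The cluster probability is a·d/b and the individual probability is c/a. The individual weight is the inverse of their product. Here a is the cluster's population, b the district total, d the number of clusters drawn in the district, and c is "the predetermined number of individuals to be sampled from the cluster". There is one c per cluster, with no index for age or household.
- **Stage 3: selection of households.** The cluster's household list is put in random order and the first 40 are taken, with more added if too few eligible children are found.
- **Stage 4: selection of children.** Each cluster supplies 70 children: 10 under 1 year, 40 aged 1–4, 10 aged 5–9 and 10 aged 10–14. One child per cohort is picked at random in a household, so that "no more than one child from each age group is chosen from the same household".
- **Descriptive analysis.** Weights start from inverse selection probabilities. The section adds that they "will be adjusted to account for differences between the projected and actual population sampled per age group in each cluster". No formula is given.

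**The concern.** A probability of c/a is right only if every child in the cluster has the same chance of selection. Under Stages 3 and 4 the chance depends on the child's age cohort, through the quota, and on how many same-cohort children share the household. Two distortions follow.

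1. **Age.** The quotas do not follow the population's age structure, so estimates pooled over age are distorted unless a later step repairs this.
2. **Household.** A child who is one of m in a household cohort has 1/m the chance of a child who is alone in it. The printed weight treats both alike.

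At stake are the weighted overall, HDSS, district, ward and age-specific seroprevalences, which serve the first primary objective. The Background gives 92–95% as the immunity level needed against measles, so an error of a few points can change how an area is judged.

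**Working it through.** **1. Plan's own figures.** 10 + 40 + 10 + 10 = 70, and 70 × 25 = 1,750. Both reproduce.

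**2. Printed weight.** (a·d/b) × (c/a) = c·d/b, so the weight is b/(c·d). With c = 70 this is b/(70·d), one constant per district. Check with illustrative b = 20,000 and d = 5: the weight is 57.14 for a = 200, 1,000 and 5,000.

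**3. Probability implied by Stages 3 and 4.** For cohort g in household h, let q_g be the number of cohort-g children recruited in the cluster, K_g the number of households in the cluster with at least one such child, and m_hg the number of cohort-g children in that household. Then P_indiv ≈ (q_g/K_g) × (1/m_hg). The weight becomes b·K_g·m_hg/(a·d·q_g), which varies by age and household.

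**4. Age imbalance.** Both sites pooled, from Population projection: under 1 year 3,223 + 944 = 4,167; 1–4 years 25,608 + 8,111 = 33,719; 5–9 years 14,597 + 4,803 = 19,400; total 57,286.

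| Under-10s | <1 | 1–4 | 5–9 |
|---|---|---|---|
| Population share | 7.3% | 58.9% | 33.9% |
| Sample share (10:40:10) | 16.7% | 66.7% | 16.7% |
| Weight needed relative to constant | 0.44 | 0.88 | 2.03 |

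The 10–14 population is not given. Assuming 0.5 to 1.5 times the 5–9 count, the relative weights are 0.34–0.44, 0.68–0.88, 1.57–2.03 and 1.01–2.36.

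Effect on an all-age estimate if age is not repaired, with **assumed** seroprevalence by cohort:

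| Assumed profile (%) | Constant weight | Age-correct | Gap (points) |
|---|---|---|---|
| 70/85/85/90 | 83.6% | 84.8–86.0% | 1.2–2.4 |
| 55/80/90/95 | 80.0% | 83.5–86.1% | 3.5–6.1 |
| 50/70/90/95 | 73.6% | 78.2–82.0% | 4.6–8.4 |
| 50/85/92/95 | 82.4% | 88.5–89.0% | 6.1–6.6 |

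The first three rows use all 4,167 infants and the three assumed sizes for ages 10–14. The last row takes 10–14 equal to 5–9 and counts only 4,167/4 ≈ 1,042 to 2,000 infants as eligible, since those under 9 months are not. The 8.4 arises only with the steepest profile and the largest 10–14 population; every other combination lies between about 1 and 7. No profile lets seroprevalence fall with age.

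**5. Household factor.** Assume 45/30/15/10% of households with a cohort child hold 1/2/3/4 such children.

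- Mean m per household, as sampled: 0.45 + 0.60 + 0.45 + 0.40 = 1.90.
- Mean of m²: 0.45 + 1.20 + 1.35 + 1.60 = 4.60.
- Mean m per child in the population: 4.60/1.90 = 2.42.
- Bias = (2.42 − 1.90) × fall per extra child = 0.52 × fall.

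A fall of 0, 1 or 4 points per extra child gives 0, 0.5 or 2.1 points too high. For 92/88/84/80% this is 88.4% against 86.3%. A rise instead of a fall reverses the sign. Other assumed splits give similar multipliers: 50/30/20% gives 3.5/1.7 − 1.7 = 0.36, and 30/30/20/20% gives 6.5/2.3 − 2.3 = 0.53.

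**6. Can the stated adjustment repair this?** A factor per age group and cluster is the same for all children in that cell, whereas m varies between households inside it. The adjustment can move cells against each other but cannot re-weight within them.

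**7. Side check.** Stage 2 keeps clusters with as few as 40 children. If a counts children, c/a runs from 70/69 = 1.01 to 70/40 = 1.75 for clusters of 69 down to 40, which cannot be a probability.

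**The case against.** **The Stage 2 formula may not be the final weight.** It stands under cluster selection, and Descriptive analysis adds an adjustment by age group and cluster. Read as post-stratification to the projected population, that adjustment corrects the 10:40:10:10 imbalance. Read as correction for shortfall against planned numbers, it is about 1 when quotas are met and the imbalance stays. The text does not settle which. This objection stands: a reader might infer that the planned estimates are about 6 points too low, but the documents do not support that as a property of the final analysis.

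**A constant weight per district is not itself an error.** It is the usual result of selection proportional to size with a fixed take per cluster. This also stands. The fault is that c/a does not describe the later stages.

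**The household bias has no documented size.** The documents give neither same-cohort children per household nor seroprevalence by household composition. This stands as to size and sign, not as to the missing factor.

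**The reach is limited.** Age quotas do not distort estimates within one cohort, including the 1–4 group that the study is powered on. Main analysis does not say whether the additive and spatial models use the weights, or which seroprevalence estimates enter the outbreak simulations. A reader might infer that these carry the bias too, but the text does not establish it.

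**A condensed article may leave the weight formula to a fuller document.** This does not dispose of the point, because the article prints a formula, calls it the weight for each individual, and the formula disagrees with the article's own Stages 3 and 4.

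**Conclusion.** The point holds in this form. The printed individual probability is not the one that the sampling procedure produces. The age part is an ambiguity: if the adjustment is only for shortfall, age-pooled estimates are biased by about 1 to 7 points under most illustrative profiles (8.4 at the extreme); if it is post-stratification, this part is repaired. The household part remains under either reading. It affects the design-based estimates, age-specific ones included, by about 0.5 points per 1-point fall in seroprevalence per extra same-cohort child on the assumed split. It is zero if there is no gradient. All seroprevalence profiles, household splits and the 10–14 population are assumptions. The case for correction is that the formula is wrong as written, serves the first primary objective and is cheap to put right.

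**What to change.** 1. Replace P_indiv = c/a by (q_g/K_g) × (1/m_hg), defined by cluster, age cohort and household. Take m_hg from the Stage 4 list of eligible children in selected households, and keep that list with the data. Count K_g from the HDSS database; the article does not say that Stage 3 already extracts it.
2. State the Descriptive analysis adjustment as calibration to projected HDSS age-group totals, counting only infants from 9 months in the youngest group.

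**Cost.** No new fieldwork: a change of formula and two roster counts. The statistical price is variance. On the assumed 45/30/15/10% split the Kish factor is 4.60/1.90² = 4.60/3.61 = 1.27, about 27% more variance. The 40 × 25 = 1,000 children aged 1–4 would then count as about 785 before clustering. Trimming extreme weights limits this but lets back some of the bias, so the trimming rule should be fixed in advance.

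### The cluster selection probability a·d/b can exceed 1, and the plan has no certainty-cell or repeat-hit rule: any selected cell larger than its district's sampling interval and sampled once would be under-weighted in the survey estimates

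*Protocol article*

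**What the plan says.** Protocol article, Stage 2 (selection of clusters), defines a as "the population size of the cluster", b as the district's cumulative population, d as the number of clusters to be drawn in the district and c as the number of individuals to be taken from the cluster. The interval is SI = b/d with a random start, and "clusters are selected according to the arithmetic progression". "The probability of selecting a cluster" is given as a·d/b, that of an individual within it as c/a, and the weight is the inverse of their product. Cells with fewer than 40 children are dropped from the frame. There is no rule for cells that are too large.

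Stage 4 says "70 children per cluster will be sampled from these households according to the following age group allocation" and arrives at 1,750 children from 25 clusters. Stage 2 ends with "Figure 3 shows the map of the 25 selected clusters from the BHDSS and FHDSS".

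The Descriptive analysis section applies the inverse-probability weights in the survey package, for overall, site, district, ward and age estimates. It says they will be "adjusted to account for differences between the projected and actual population sampled per age group in each cluster". It does not say how.

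**The concern.** In systematic sampling proportional to size, a·d/b is the expected number of hits on a cell. It equals the inclusion probability only up to a = SI. Above that the cell is certain to be selected, its inclusion probability is 1, and dividing by a number above 1 makes its children count for too little.

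The design leaves room for this. The sampling units are fixed 25 km² squares that pool every settlement inside them, so their populations are not controlled, and d is small in each district. An affected cell would be the most populous in its district. Results are to be reported by district, and the Background cites a 92–95% immunity requirement, so an error of one or two points in a district would matter to the reading.

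**Working it through.** **The plan's own figure.** 25 × (10 + 40 + 10 + 10) = 25 × 70 = 1,750, as stated. This total leaves no room for a second set of 70 from one cell unless that cell is counted twice among the 25.

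**Weight algebra (Stage 2 formulas).** Weight = 1 / [(a·d/b) × (c/a)] = b/(d·c). The size a cancels. Seventy children at this weight sum to b/d = SI, whatever the size of the cell.
- If a ≤ SI, this is correct.
- If a > SI and c children are taken once, the inclusion probability is 1 and the correct weight is a/c. Formula over correct = [b/(d·c)] / (a/c) = b/(a·d).
- Assumed examples: 40% share, d = 3: 1/1.2 = 83% of the correct weight. 50%, d = 3: 1/1.5 = 67%. 30%, d = 5: 1/1.5 = 67%.

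**Scale of SI (Population projection section, children aged 9 and under, January 2023).** 43,428 + 13,858 = 57,286, and 57,286/25 = 2,291 per cluster. Proportional sharing gives 25 × 43,428/57,286 = 18.95 clusters for the Basse site (four districts, 4–5 each) and 6.05 for the Farafenni site (two districts, about 3 each). Mean village size is 43,428/220 = 197 and 13,858/149 = 93. A cell would need about 12 average Basse villages (2,291/197), about 25 average Farafenni villages (2,291/93), or one large settlement, to exceed the interval. The equal split between districts is my assumption.

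**Shift in the district estimate.** Let s be the cell's share of the district and assume a 10-point immunity difference between it and the rest.

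*All d selected cells distinct.* The cell counts as 1/d, so the shift is (s − 1/d) × 10 points.
- d = 3: s = 0.40 gives 0.7; s = 0.60 gives 2.7.
- d = 5: s = 0.30 gives 1.0.

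*Averaged over draws, each distinct cell sampled once.* For P = s·d between 1 and 2, there is one hit with probability 2 − P (cell counts as 1/d) and two hits with probability P − 1 (cell counts as 1/(d − 1)).
- d = 3, s = 0.40 (P = 1.2): 0.8/3 + 0.2/2 = 0.367; shift 0.33 points.
- d = 3, s = 0.60 (P = 1.8): 0.2/3 + 0.8/2 = 0.467; shift 1.33 points.
- d = 5, s = 0.30 (P = 1.5): 0.5/5 + 0.5/4 = 0.225; shift 0.75 points.

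**Simulation check** (20,000 systematic draws per scenario; assumed 80% immune in the large cell, 90% elsewhere).
- s = 0.50, d = 3: truth 0.850, single take 0.858, k × 70 children for k hits 0.850.
- s = 0.30, d = 5: truth 0.870, single take 0.8775, k × 70 children 0.870.
- s = 0.33, d = 3 (P = 0.99): no bias.

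**Overall estimate.** A three-cluster district is about 3/25 = 12% of the total, so 0.7–2.7 points becomes about 0.1–0.3.

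**The case against.** The strongest reply is that nothing shows the condition is met. This stands. Without cell sizes, district totals or d per district, a reader might infer that the largest cells *are* under-weighted, but the documents support only that they would be if one exceeds SI. Putting a probability on it does not help: with assumed lognormal village sizes (log SD 0.5–1.25, 12–30 populated cells per district) the chance that some district has such a cell runs from 0.3% to 99%.

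Second, the weight is unbiased if a cell hit k times yields k × 70 children. That is true, and the simulation confirms it. The text states no such rule, however, and a fixed 70 per cluster with 25 mapped clusters makes a single take the likelier reading.

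Third, 25 distinct cells limit the possible size. Under the stated progression a cell with a ≥ 2·SI is always hit at least twice, so distinct cells imply P below 2. A reader might carry the calculation to d = 5 with a 50% share and quote 3.0 points, but P would be 2.5 there and five distinct cells could not result. Likewise, at d = 3 and a 60% share a single hit has only 20% probability, so 2.7 points is the edge of the range.

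Fourth, the weights are specified for the survey-package estimates. The Main analysis section does not say that the additive or spatial models use them, so the point should not be extended to those models.

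Fifth, the age-group adjustment of the weights might offset part of the effect. Its wording does not establish that it removes the 1/P factor, nor that it keeps it.

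Last, certainty-cell handling could be left to a fuller document. Here, though, the article prints the complete weight formula and a lower size limit, so the formula can be judged as stated.

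**Conclusion.** The point holds conditionally. As printed, a·d/b is not bounded by 1, and no rule covers a cell that is certain to be selected or is hit more than once. If a selected cell exceeds its district's SI and is sampled once, its children are under-weighted by b/(a·d) in the design-weighted estimates.

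With a 10-point contrast assumed, a district estimate moves by about 0.3–1.3 points on average over draws (d = 3, share 40–60%) or about 0.75 points (d = 5, share 30%). Given distinct cells, the figures are 0.7–2.7 points and 1.0 point. The estimate is too high if the large cell is less immune than the rest, and too low if it is more immune. The overall estimate is affected several times less. These sizes rest on the assumed shares, contrast and d. The existence of such a cell is not shown, and if there is none there is no bias from this source.

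**What to change.** Report a, b and d for each district and check for cells with a > b/d. For each one that was selected and sampled once:
- Set P_clust = 1 (weight a/c) and declare the cell a certainty stratum in the survey design object.
- Weight the m other selected cells in that district to the remaining population, so each child there has (b − a)/(m·c), with m the number of non-certainty cells actually selected.

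Capping P_clust at 1 alone is not enough when the cells are distinct. With d = 3 and a 50% share, the capped cell counts as 0.5/(0.5 + 2/3) = 0.429, giving 0.857 against a truth of 0.850. The uncapped formula gives 0.9 − 0.1/3 = 0.867, so about 40% of the bias remains. Weighting the rest to b − a returns 0.850. Averaged over draws, capping does better (0.849 against 0.850), but it is the sample actually drawn that is analysed.

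If a cell hit k times did contribute k × 70 children, keep the stated weight and say so.

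The cost is one check of a frame the sponsor already holds and a small change to the weighting code, with no new field work. Weights become slightly more variable. If no cell exceeds SI, one sentence saying so closes the point.
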